**Fig 3 pone.0273239.g003:**
[figure not shown]
Integration of PAR into the SEL intervention–the iterative reflective inputs and feedback from teachers during their training sessions will be integrated into the planning of subsequent training sessions throughout the intervention period.

**Fig 4 pone.0273239.g004:**
[figure not shown]
Project flow and assessment schedule for research data collection.

#### Impact of COVID-19

The SEL-PLA training for teachers and the SEL-PLA with the students were initially planned to be implemented as in-person classroom sessions. Due to COVID-19, lockdowns were imposed and the CLC was forced to move some of their lessons online. The SEL-PLA sessions (both teacher training and student sessions) now incorporate adaptations that can be implemented online. Materials are digitally sent and accessible online. Lessons are redesigned in bite-sized sessions that incorporate interactive and participatory elements to engage the teachers. These resources will be uploaded on a Learning Management System. Although the resources can be accessed asynchronously, the session itself will be run synchronously. Zoom provides common platform for the synchronous sessions. The measurements needed for the evaluation too will shift to use more digital devices, with minimal physical contact.

### 2.6 Participants

#### 2.6.1 Sample

**Participants are from a community learning centre (CLC).** The CLC involved in this programme is located in urban settings in Kuala Lumpur, the capital city of Malaysia. Established in March 2007, the centre was set up to provide education for the children from Myanmar refugee families. Classes ranged from pre-school to secondary school. In the year 2021, there were 16 teachers and 215 students enrolled for the academic year.

#### 2.6.2 The teachers

All teachers from the school (at current baseline, n = 16) will be invited to participate. Teachers will be enrolled into the study if they are willing to provide informed consent and agreeable to commit for the full duration of the programme.

#### 2.6.3 The students and parents

All students aged 6 to 19 still enrolled in the academic year of 2022 will be invited to participate. Students who are willing to provide assent and whose parents or caregivers are willing to provide informed consent will be enrolled into the evaluation. We are aware that there may only be a small number of students that will be part of the collected data at this early stage and also the limited timeframe to observe the effects of the intervention. We intend to plan a full-scale randomised trial once we have as a follow up to this study; hence, there were no power calculations of sample size at this stage. Nevertheless, for a study with an effect size of 0.3 (as per studies in the literature) [15] and a power of 80%, a sample size of at least 90 students would be needed to test the association at 5% levels using two tailed test.

### 2.7 Data collection, measures, outcomes

A mixed methods approach allows a deeper as well as a more comprehensive analysis [39] of this multipronged complex intervention. A concurrent mixed-method design [40] will be employed for this evaluation. Qualitative and quantitative data will be collected concurrently and triangulated.

#### 2.7.1 Primary outcomes and assessment measurement

Feasibility assessment.

Acceptability

In depth interviews and focus group discussions will be conducted with the teachers to assess their perceptions and thoughts about the intervention and its implementation at scheduled timepoints (see Fig 4), specifically focusing on:

What are the barriers and facilitators to implementing the activities with their students?Do the teachers see value in the programme as it was delivered?What is the proportion of eligible students who participated in the SEL-PLA sessions with their teachers? (we define an acceptable range as 70% and above)

Implementation

The implementation and process evaluation will be performed during the entire duration of the SEL programme. During the implementation of the structured SEL-PLA activities for students, a trained observer from the programme team will be attending the sessions. The observer will complete a Lesson Observation form collecting information on the following:

adherence to the intended activitiesthe quality of the deliveryteacher and student engagement during the activitiesduration of the activities (dosage)any adaptations performed

Teachers will also be asked to complete self-report logs on the extent of their implementation with the students documenting the following details:

adherence to the intended activitiesstudent attendance and participation levels during the activitiesduration of the activities (dosage)any adaptations performed

Changing needs, resources and support requested by teachers.

SEL needs assessment and contextual factors will be collected via the SEL needs assessment survey from School Connect [41], the Safe, Inclusive, and Respectful Climate survey [42] and focus group discussions with teachers. The SEL needs assessment survey is designed to be a pre-intervention assessment of overall school climate and students’ SEL skills scale and the Safe, Inclusive and Respectful Climate survey measures the degree to which teachers perceive their school’s environment to be safe and inclusive for their students. SEL needs of the teachers will also be monitored using a WhatsApp chatgroup platform established for this project. Reflective open-ended questions integrated into training sessions will also be used to document and support teacher’s needs.

Our definition of successful implementation would focus on the adherence to the intended activities that were implemented (the fidelity), of at least 70% and dosage executed (at least 70% of the total planned duration).

#### 2.7.2 Secondary outcomes (Effects)

*Student resilience*, *academic performance*, *SEL competencies*, *mental health status*. Resilience will be measured using the Child Resilience Questionnaire, a multi-domain measure of resilience developed by The Childhood Resilience Study [43]. This scale measures five domains of individual (self) and environmental (school and friends, family, and culture) components associated with resilience.

Academic achievement will be assessed using the Academic Performance subsection scores from the teacher report of the Social Skills Improvement System Rating Scales (SSIS) [44]. SSIS is a scale that measures Social Skills, Problem Behaviours and Academic Competence. The average grade point of each student will also be obtained from their school records.

SEL competencies will be measured using pre/post-tests to be administered after SEL-PLA activities are implemented, supplemented by the SSIS [44] subsections in Social Skills, collected from students, teachers and parents.

Mental health of the students will be assessed using the Strengths and Difficulties Questionnaire [45,46], which is a screening tool for psychological adjustment in children and aims to detect emotional or behavioural problems. Data will be collected from teachers, students and parents.

In addition, focus group discussions with teachers will also be used to elicit observed differences in their students before, during and after the implementation of the SEL-PLA activities. Given the limited time teachers have to implement the student SEL-PLA (due to COVID-19 restrictions and lockdowns), quantitative effects may not be immediately measurable. Hence, qualitative observations of the effects of the SEL activities will be elicited from focus group discussions with the teachers as well.

*Teacher mental health status and SEL competencies*. Mental Health will be measured using the Depression Anxiety and Stress Scale, 21-item version (DASS-21) [47]. DASS-21 has three subscales that measures depression, anxiety and stress symptoms in an individual.

Teaching competencies for SEL will be measured using pre-post assessments to be administered at every teacher training session. Focus group discussions with teachers will held at intervals of the study to elicit on their perception of their own SEL competencies, areas to improve on and their confidence in providing a supportive SEL environment for their students.

*Other covariates and factors for the testing of theory*. Other covariates and factors like the changes in the school climate and changes in relationships and social support network of the student will also be monitored. The Safe, Inclusive, and Respectful Climate survey [42] will be used to monitor teachers’ perceived changes in the school environment at the beginning, middle and end of the study. Changes in relationships and social support network will be elicited from periodic focus group discussions with teachers and documented qualitatively.

The relationship between SEL competencies, resilience and academic performance will also be tested.

#### 2.7.3 Assessment schedule

The assessment schedule for research data collection activities is shown in Fig 4.

### 2.8 Data analysis

#### 2.8.1 Quantitative data

For all quantitative data, descriptive statistics will be run with continuous variables summarized using means and standard deviations and categorical variables summarized using frequencies and proportions.

The assessment of intervention implementation will be using the summary measures collected from observations and self-reports.

For the assessment of impact, we will analyse scores from the respective instruments to estimate if there are differences before and after the intervention using T-test, Wilcoxon rank sum test, one-way repeated measures ANOVA or the Friedman Test, depending on whether the data obtained fulfilled the assumptions required for the different type of analyses.

Further, path analysis will be used to test for mediators and moderators of SEL competencies and the relationship with resilience and academic performance in students.

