## 2. Methods

### 2.1 Aims and objectives

The aim of the study is to evaluate the feasibility of a complex intervention on social and emotional learning, focused on increasing resilience and academic performance in refugee children in the context of a community learning centre. The study also aims to evaluate the effects of the SEL intervention on students and teachers in the CLC.

Our primary research question is:

Is PARSEL feasible in the context of CLC in terms of acceptability and implementation, from the perspective of teachers?

Our secondary research questions are:

Does PARSEL have any effects in improving resilience and academic performance in refugee students?Do any of the proposed mechanisms in the conceptual framework explain the link between the programme, resilience and academic achievement? (Was the theory of change realised in the study design?)

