### 2.4 Study design

A pre-post single arm design combined with qualitative and quantitative methods will be used to address the research questions (see Table 1).

**Table 1 pone.0273239.t001:** Methods, data collection instruments and data source according to research questions.

Research Question	Data collection Instruments	Data Source
1. Is PARSEL feasible in the context of CLC in terms of acceptability and implementation, from the perspective of teachers? a. Acceptability b. Implementationi. i. Fidelity ii. Changing needs and support throughout the programme	Focus group discussion (FGD) In depth Interviews Lesson observations Teacher self-report log Focus Group Discussion (FGD) Focus group discussion (FGD) WhatsApp group Reflective open-ended questions and journaling SEL Needs assessment survey Safe, Inclusive, and Respectful Climate survey (School Climate Survey) [39]	Teachers Teachers Programme team Teacher Teacher Teacher Teacher Teacher Teacher Teacher
2. What is the impact of the programme on: a. Student resilience and academic performance b. Student SEL competencies c. Student mental health status d. Teacher mental health status e. Teacher SEL competencies	Child Resilience Questionnaire Student academic grades Social Skills Improvement System Rating Scale (SSIS) [38] Focus group discussion (FGD) SDQ [36] Depression, Anxiety and Stress Scale, 21 items (DASS-21) [37] Pre post tests In depth interviews	Students, Teachers, Parents Teachers Students, Teachers, Parents Teachers Students, teachers, parents Teachers Teachers Teachers
3. Do any of the proposed mechanisms in the conceptual framework explain the link between the programme, resilience and academic achievement? Was the theory of change realised in the study design?	Safe, Inclusive, and Respectful Climate survey (School Climate Survey) [39] Focus group discussion (FGD) Child Resilience Questionnaire Student academic grades Social Skills Improvement System Rating Scale (SSIS) [38]	Teacher Teacher Student, Parent, Teacher Teacher Student, Parent, Teacher

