#### Component 4: Mental health surveillance for students

The fourth component involves mental health surveillance for the students in the programme. The mental health of the students will be assessed at several timepoints of the programme.

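### For impact outcomes with three or more time points, the named repeated measures ANOVA and Friedman tests do not test the stated before-after difference

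*Protocol article*

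**What the plan says.** Section 2.4 sets the design: "A pre-post single arm design combined with qualitative and quantitative methods will be used". Section 2.1 asks a directional question: "Does PARSEL have any effects in improving resilience and academic performance in refugee students".

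For the assessment of impact, section 2.8.1 will "estimate if there are differences before and after the intervention using T-test, Wilcoxon rank sum test, one-way repeated measures ANOVA or the Friedman Test", the choice "depending on whether the data obtained fulfilled the assumptions required for the different type of analyses". It names no contrast between particular assessments.

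On the number of assessments, the readable text gives the following:
- Student mental health, an impact outcome in Table 1 (question 2c): "The mental health of the students will be assessed at several timepoints of the programme" (Component 4). The number is not given.
- School climate survey: "perceived changes in the school environment at the beginning, middle and end of the study" (section 2.7.2). This is three time points, but the section treats the survey as a covariate, and Table 1 lists it under questions 1 and 3 rather than under impact.
- Resilience, grades and the other instruments: the schedule is in Fig 4, which is not shown.

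**The concern.** A before-after question concerns one difference, last minus first. The one-way repeated measures ANOVA and the Friedman test have as their null that the outcome is the same at every time point. They carry no direction and reject for any departure, including a dip in the middle that has fully recovered by the end.

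Such a dip is plausible here. The article describes lockdowns, a move to online sessions and limited time to deliver the student sessions. If an omnibus p-value is reported as the result of the before-after analysis, it can be small when start and end are equal. When it is small for another reason, it still does not say whether students improved. The Discussion says the data will help to design a cluster randomised trial, for which an estimated change with its interval is more useful than a non-directional p-value.

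**Working it through.** **Inputs from the protocol article.** Effect size 0.3, power 80%, two-sided 5% and 90 students (section 2.6.3); 215 students enrolled (section 2.6.1).

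**Assumptions not in the documents.** Three time points, normal data and compound symmetry. The SD of a paired change is set to 1, so the residual variance is σₑ² = 0.5, because the variance of a difference is 2σₑ². The size of the middle shift is also assumed, so a range is shown.

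**Step 1: reproduce the plan's figure.** The paired formula gives n = ((1.960 + 0.842)/0.3)² = 87.2, so 88 by normal approximation. The exact paired t-test gives power 0.799 at n = 89 and 0.804 at n = 90. The plan's 90 therefore reproduces as a two-time-point paired comparison.

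**Step 2: before equals after, middle shifted.** The ANOVA noncentrality is λ = n·Σ(μⱼ − μ̄)²/σₑ². For means (0, 0.3, 0), μ̄ = 0.1 and the sum of squares is 0.01 + 0.04 + 0.01 = 0.06. At n = 90, λ = 90 × 0.06/0.5 = 10.8. With 2 and 178 degrees of freedom the critical F is 3.05, and the test rejects with probability 0.84. The direction of the shift does not matter. The first-versus-last difference is zero, so a paired test of it rejects 5% of the time.

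| Middle shift | n | ANOVA | Friedman (simulated) | Paired first-last |
|---|---|---|---|---|
| 0.2 | 90 | 0.48 | not run | 0.05 |
| 0.3 | 90 | 0.84 | about 0.70 | 0.05 |
| 0.5 | 90 | >0.99 | 0.99 | 0.05 |
| 0.2 | 215 | 0.87 | not run | 0.05 |

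With all three means equal, every test holds about 5% in simulation.

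**Step 3: a real gain of 0.3.**
- Steady, (0, 0.15, 0.3), n = 90: the sum of squares is 0.045 and λ = 90 × 0.045/0.5 = 8.1. The paired test has the same noncentrality, 90 × 0.3² = 8.1, but spends one degree of freedom instead of two. Power is 0.72 for ANOVA against 0.80. ANOVA needs about 109 students for 80%.
- Late, (0, 0, 0.3), n = 90: the sum of squares is 0.06 and λ = 10.8. Power is 0.84 for ANOVA against 0.80.
- Steady, n = 215: 0.98 against 0.99.

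**Step 4: rank tests compared like with like** (simulation, 10,000 replicates, n = 90). For the steady gain, Friedman has about 57% against 79% for a signed-rank test of last versus first. For the late gain it has about 70% against 79%.

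**Step 5: two time points.** The repeated measures ANOVA is then the paired t-test (power 0.804 at n = 90), and the problem does not arise.

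**The case against.** The strongest reply is that section 2.8.1 is one condensed sentence in a journal article, and that follow-up contrasts are normally left to an analysis plan, which is not shown. A contrast may be added there. But the published sentence already assigns omnibus tests to a before-after aim, so the point corrects a stated choice and does not ask for missing detail.

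Four stronger readings are tempting, and the documents do not support them.

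- *Every impact outcome is affected.* No readable section gives resilience or grades a third assessment. The only explicit three-point schedule belongs to the climate survey, which is not an impact outcome. For student mental health, more than two time points are implied but not counted.
- *The plan will declare an effect from a temporary shift.* Section 2.8.1 states no decision rule. It also promises means and standard deviations, which would show a reader that start and end agree. The rejection rates say what the test does, not what the investigators will conclude.
- *Assumption checks will decide between t-test and ANOVA.* The wording is loose enough to allow this. The ordinary reading is that the number of time points picks the pair of tests and assumptions choose within the pair.
- *The omnibus tests generally cost power.* For ANOVA this depends on the shape of the gain. Student sessions start only after at least 7 months of teacher training (Component 3), so a late gain is as plausible as a steady one.

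The Friedman comparison rests on normal data, whereas the plan would use that test when parametric assumptions fail. Part of its deficit is the inefficiency of its within-student ranks, not the omnibus null alone. Finally, these are secondary outcomes of a single-arm feasibility study. The primary feasibility criteria are untouched.

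**Conclusion.** The point holds for any impact outcome with three or more time points, and only there. For such an outcome the named ANOVA and Friedman tests answer whether anything varied over time, not whether after differs from before. A middle-only shift of 0.3 at n = 90 makes them reject about 84% and 70% of the time when the before-after difference is zero. The rate varies with the shift (48% for ANOVA at 0.2) and rises with sample size.

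The power consequence is secondary. ANOVA loses about 9 points for a steady gain at n = 90 (0.804 − 0.716), gains slightly for a late one, and is nearly equal to the paired contrast at n = 215. At n = 90 Friedman loses about 22 points (79 − 57) and 9 points (79 − 70) against a signed-rank first-last test. All of this rests on the assumptions listed in the working. The change should be made because it is cheap and aligns the test with the question, but it does not threaten the feasibility objective.

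**What to change.** In section 2.8.1:
1. State that the before-after result for each impact outcome is one prespecified contrast, last post-programme assessment minus first assessment, reported with its estimate and 95% CI.
2. Where there are three or more time points, take this contrast from the repeated-measures model or from a paired comparison of first and last, using the signed-rank test if the data are not normal.
3. Keep the omnibus ANOVA or Friedman p-value only as a description of the time course.
4. Word test selection so that assumption checks choose only between the parametric and rank versions of the same comparison.

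The cost is a few sentences of analysis wording and no extra data. The downside is that a transient mid-programme change is described and no longer counts as an effect.

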## Abstract

This paper describes a protocol for the feasibility evaluation of the Participatory Action Research on Social and Emotional Learning (PARSEL) programme. PARSEL aims to contribute towards the development of academic achievement and resilience among urban refugee students in a community learning centre in an upper middle-income country. The evaluation is a single arm pre-post design using a mixed methods approach, with the main focus on the feasibility of the programme. Measurements of impact are also included as the secondary outcomes of the study. The programme aims to enrol students from refugee background in a community learning centre. The programme is estimated to run for 18 months and the study is due to report in the end of fourth quarter of 2022.

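### The rank test named for before-after comparisons is the independent-samples Wilcoxon rank sum test, which does not fit a single-arm pre-post design and contradicts the plan's own paired methods

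*Protocol article*

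**What the plan says.** Section 2.4 sets the design: "A pre-post single arm design combined with qualitative and quantitative methods". There is no comparison group.

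For the assessment of impact, section 2.8.1 will look for "differences before and after the intervention using T-test, Wilcoxon rank sum test, one-way repeated measures ANOVA or the Friedman Test", with the choice "depending on whether the data obtained fulfilled the assumptions required for the different type of analyses".

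Section 2.6.3 says that "there were no power calculations of sample size at this stage". It then gives an indicative figure for an effect size of 0.3 and 80% power: "a sample size of at least 90 students would be needed to test the association at 5% levels using two tailed test".

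The abstract sets the rank of these analyses: "Measurements of impact are also included as the secondary outcomes of the study". The primary question is feasibility.

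**The concern.** The Wilcoxon rank sum (Mann-Whitney) test assumes two independent samples. Here each after score comes from a person who also gave a before score, and the analysis section describes no comparison of independent groups. The rank test for two measurements on the same people is the Wilcoxon signed-rank test.

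One-way repeated measures ANOVA and the Friedman test, named in the same sentence, are dependent-sample methods, so the list is inconsistent.

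An unpaired test uses a standard error that ignores the covariance between before and after scores. When that covariance is positive, the standard error is too large. The test then rejects too rarely under the null and misses real change. The estimated change itself is unaffected; what suffers is the P value and the conclusion drawn from it. Section 3 says that the data will feed the design of a cluster randomised trial, so a missed signal could carry forward.

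**Working it through.** **Inputs.** From the article: single arm, pre-post (2.4); effect size 0.3, 80% power, two-sided 5%, at least 90 students (2.6.3). Assumed, because the article is silent: the pre-post correlation ρ, bivariate normal scores, equal SD before and after, and whether 0.3 is in raw-score SDs or is a standardised mean change. That scores are linked by person is inferred from the design and the repeated-measures methods; it is not stated for each instrument.

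**Step 1: reproduce the 90.** With z-values 1.96 and 0.842, (1.96 + 0.842)² ≈ 7.85.

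| Reading of the effect size 0.3 | Calculation | n |
|---|---|---|
| Paired t-test, standardised change 0.3 | noncentral t | 90 (power 80.4%) |
| Paired, normal approximation | 7.85 / 0.09 | 88 |
| Correlation of 0.3, Fisher z | 7.85 / 0.3095² + 3 | 85 |
| Two independent groups | 2 × 7.85 / 0.09 | 175 per group |

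Of these readings, only the paired t-test gives 90. The sample-size sentence therefore presupposes pairing, which the named rank test discards.

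**Step 2: type I error when pairing is ignored.** The unpaired statistic takes the variance of the mean difference as 2σ²/n, but the true variance is 2σ²(1−ρ)/n. Under the null the statistic therefore has SD √(1−ρ), and the actual two-sided error is about 2[1 − Φ(1.96/√(1−ρ))]:

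- ρ = 0.3: 1.96/0.837 = 2.34, error about 1.9%
- ρ = 0.5: 1.96/0.707 = 2.77, error about 0.6%
- ρ = 0.7: 1.96/0.548 = 3.58, error about 0.03%

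This formula is for the unpaired t-test, which the rank sum test follows closely. Simulation of the rank sum test itself (2,500 to 8,000 replicates per setting) gave about 2-3%, 0.6-0.8% and 0%.

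**Step 3: power, 90 pairs, shift of 0.3 raw SD (simulation).**

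| Assumed ρ | Rank sum | Signed-rank | Relative loss |
|---|---|---|---|
| 0 | 50% | 50% | nil |
| 0.3 | 49% | 63% | 14/63 = 22% |
| 0.5 | 50% | 78% | 28/78 = 36% |
| 0.7 | 50% | 95% | 45/95 = 47% |

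Rank sum power stays near 50% because its expected statistic, about 0.3 × √(90/2) = 2.01 on the t-test scale, lies close to the critical value 1.96 whatever ρ is. The signed-rank test gains because the SD of the change, √(2(1−ρ)), shrinks as ρ rises.

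**Step 4: the other reading, 0.3 as a standardised mean change.** Signed-rank power is then about 77-79% at every ρ. Rank sum power is about 78% at ρ = 0, 65% at 0.3, 49% at 0.5, 39% at 0.6, 23% at 0.7 and 7% at 0.8. The unpaired t approximation Φ(0.3√90 − 1.96/√(1−ρ)) agrees: 0.53 at ρ = 0.5 and 0.23 at ρ = 0.7. On this reading the loss reaches half of the paired power at about ρ = 0.6.

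**The case against.** The best defence is that this is a naming slip. Two of the four methods are within-person methods, and the 90 is a paired figure, so the authors evidently mean to analyse change within people. That is probably right. It is a reason to expect a sensible analysis, not a reason to leave the wrong test in the published plan: an analyst who follows the text uses a mis-sized test, and one who does not has an unexplained deviation.

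The exposure is also narrower than it looks. A reader might infer that any failure of normality leads to the wrong test. The text does not support that: the choice among four tests depends on the data, and Friedman is available as a non-parametric option. Section 2.5 has student mental health assessed at several timepoints, and section 2.7.2 has the climate survey at three. The rank sum test would arise for non-normal measures with two timepoints. Section 2.7.2 does describe pre/post tests of SEL competencies, for students and for teachers, so such measures exist. The full schedule is in Fig 4, which is not available here.

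A reader might also infer that most of the power would be lost. The documents give no correlation to support this. With 0.3 in raw SDs, the loss stays below half over the range examined; it exceeds half only from about ρ = 0.6, and only if 0.3 is a standardised change.

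That the T-test is not labelled as paired is no error in itself. A condensed article may leave that to the full plan, and the paired reading is the natural one.

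Finally, with positive correlation the error is conservative, so it would not create a false claim of benefit. The feasibility criteria (70% participation, adherence and dosage, with interviews and focus groups) do not use this test. Both points stand and lower the severity.

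**Conclusion.** Wrong as written, of moderate severity. The article names an independent-samples test for within-person comparisons, against its own dependent-sample methods and its own indicative sample size. This part rests on the text and needs no assumption beyond linkage of scores by person.

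The size of the effect is conditional. If the rank sum test were used, the power loss at 90 pairs and a 0.3 raw-SD shift would run from nil at correlation 0, through about 28 percentage points at 0.5, to about 45 points at 0.7, with type I error well below 5% from 0.5 upward. Those figures rest on assumed correlations and normal scores. No figure is offered for the 16 teachers, because the article gives no effect size for them.

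The consequence is a possibly missed signal in a secondary outcome of a feasibility study. It does not threaten the primary question.

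**What to change.** In section 2.8.1, name the paired t-test and the Wilcoxon signed-rank test for measures with two timepoints, in place of the unlabelled T-test and the rank sum test. Keep repeated measures ANOVA and Friedman for measures with three or more.

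The cost is one line of wording in the protocol or analysis plan. It needs no extra participants or assessments. It does require that before and after records carry the same participant identifier, which the repeated-measures methods already need.
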